## Methods/Design

This study used a randomized controlled design with three arms: control, the original PACE intervention, and PACE Plus intervention (enhanced with cross-cultural communication training) to test the comparative effectiveness of PACE with cross-cultural communication training, a proven asthma-based communication intervention for physicians. All study procedures were reviewed and approved by the University of Michigan Health Sciences and Behavioral Sciences Institutional Review Board (IRB-HSBS HUM#00030087).

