### Sample size determination

The sample size of 1002 children and their parents total at baseline was determined by power calculations using the primary outcome of proportion of subjects with emergency department (ED) visits in the last twelve months taking into account a 25% attrition rate over 24 months leaving 801 total subjects at the end of the study. The sample size calculation is based on the assumption that the clustering of patients within physician practices is negligible, which is justified from the previous PACE study [14]. In that prior research, the intracluster correlation values were close to zero (0.24 at the physician level; 0.003 at the site level). In analysis, such correlation will be adjusted for, if necessary. In the previous PACE study [14], the baseline proportion of patient participants with an ED visit was 30% and this was decreased by 15% in 24 months. For the current study, there will be 80% power to detect a more conservative difference of 12% or more in the proportion of patient participants with an ED visit in 24 months at the significance level of 0.05.

In the previous PACE study, those in the intervention group decreased by a little more than one mean emergency office visit and 0.09 mean hospitalizations [14]. With the sample size in the current study, there will be statistical power to detect changes at that level for hospitalization and at much lower levels than in the previous PACE study for emergency office visits. Given the relatively rare occurrence of emergency department visits, the sample size needed to detect changes is relatively large; this gives an advantage in having sufficient statistical power to detect small changes in other outcomes, including symptoms, patient satisfaction and asthma related quality of life.

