### Randomization

#### *Experimental design and randomization*

A randomized controlled design was used in this study. At the beginning of the study, a permuted block randomization schedule was created using the RAN TBL and RANUNI functions in SAS to generate blocks of two for random assignment of physicians. Data are collected from three sites, Atlanta, Georgia, New York City, New York, and cities throughout Michigan. It is recognized that geographic site as well as size of practice of the physicians selected for study could impact on results. Thus, randomization was stratified by geographic area (three levels, Atlanta area, metropolitan New York, and Michigan) and size of practice (two levels, solo practice and multiple-physician practices). This randomization ensured that each type of practice and geographic area would be evenly distributed across the three arms of the study, which reduces bias due to these potentially confounding factors in the comparative analysis. Once physicians consented to participate, they were placed into one of the three arms of the study according to the randomization schedule with 44 physicians assigned to PACE, 36 to PACE PLUS and 32 to control (see sample size determination) with a total of 112 physicians and 1062 patients following those physicians into randomization.

Because this evaluation is being conducted for the purpose of recommending interventions for adoption, considerations about external validity of the results are important. One strength of this sample is that it includes physicians from practices in three large metropolitan areas. Thus, although the physician sample involved is not drawn from the entire U.S. population of clinicians, the study results will be somewhat representative of a wide variety of practice sites. Further, because background and practice characteristics of participating physicians will be assessed, it will be possible to make comparisons to the broader group of clinicians practicing in the U.S., as well as judgments about the extent to which the interventions are influenced by these characteristics.

Another threat to external validity, multiple–treatment interference, will be addressed by questionnaire items that will allow us to measure whether physicians have been involved in any other professional education efforts focusing on asthma care and education and cross-cultural communication training.

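### The 80% power claim treats clustering as negligible, but the physician-level ICC printed to justify this is 0.24; at that value power for a 12-point difference is about 54% or lower

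*Protocol article*

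**What the plan says.** All of the power reasoning is in one section of the protocol article, Sample size determination. The endpoint is the "primary outcome of proportion of subjects with emergency department (ED) visits in the last twelve months". The planned size is 1002 children at baseline, "taking into account a 25% attrition rate over 24 months leaving 801 total subjects at the end of the study". For the reference rate, the section reports that in the previous PACE study "the baseline proportion of patient participants with an ED visit was 30% and this was decreased by 15% in 24 months". The claim is that "there will be 80% power to detect a more conservative difference of 12% or more in the proportion of patient participants" with an ED visit, at a significance level of 0.05. No second proportion is named.

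The section says openly that clustering of children within practices is taken as negligible. Its reason is that in the previous study "the intracluster correlation values were close to zero (0.24 at the physician level; 0.003 at the site level"). It adds that correlation will be adjusted for in the analysis if that proves necessary.

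The Randomization section makes the physician the unit of allocation, with "44 physicians assigned to PACE, 36 to PACE PLUS and 32 to control", 112 in total. Children follow their physician into the arm.

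**The concern.** The justification and the figure offered for it contradict each other. When physicians are randomized, the physician-level ICC sets the loss of information, and 0.24 is large for clusters of about seven children. The site-level value of 0.003 does not help, because sites are strata here and not randomized units.

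This is the only numeric power statement in the article, and it concerns the outcome used to size the trial. The first study question is PACE Plus against PACE. If that comparison is null, a reader will take the trial as having had an 80% chance of showing a 12-point benefit. At the printed ICC the chance was little better than even.

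**Working it through.** **Inputs.** From Sample size determination: 801 children at the end, reference rate 30%, difference 12 points, alpha 0.05, physician ICC 0.24. From the recruitment and randomization sections: 112 physicians, split 44/36/32. Assumptions, because the article does not state them: two-sided test, equal arms (801/3 = 267), equal cluster sizes, and the recruited number of physicians as the number of clusters.

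**Formula.** Normal approximation for two proportions with n per arm and p̄ = (p1 + p2)/2:

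power = Φ{ [ |p1 − p2| − 1.96·√(2p̄(1 − p̄)/n) ] / √( [p1(1 − p1) + p2(1 − p2)]/n ) }.

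With continuity correction, |p1 − p2| is reduced by 1/n.

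**Step 1: the plan's own figure, without clustering.** 30% v 42% at 80% power needs 250 per arm, or 267 with continuity correction. Then 3 × 267 = 801 and 801 × 1.25 = 1001.25, rounded up to 1002. Both planned totals come out exactly. In the direction of a fall, 30% v 18% with 267 per arm:

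- null SE √(2 × 0.24 × 0.76/267) = 0.03696; alternative SE √((0.21 + 0.1476)/267) = 0.03660
- Φ{(0.12 − 1.96 × 0.03696)/0.03660} = 90% (88% with continuity correction)

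**Step 2: design effect at the printed ICC.**

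- children per physician: 801/112 = 7.15
- design effect: 1 + (7.15 − 1) × 0.24 = 2.48
- effective number per arm: 267/2.48 = 108

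**Step 3: power with 108 per arm.** For 30% v 18%, the null SE is 0.0582 and the alternative SE 0.0576, so Φ{(0.12 − 1.96 × 0.0582)/0.0576} = 54%. Other readings of the 12 points:

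| Scenario | Power at ICC 0.24 | With continuity correction |
|---|---|---|
| 30% v 18% | 54% | 48% |
| 30% v 42% | 45% | 39% |
| 50% v 38% | 43% | not computed |

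**Step 4: actual physician split, 30% v 18%.** Children are shared out in proportion to physicians and divided by 2.48, giving effective sizes of about 127 (PACE), 104 (PACE Plus) and 92 (control). PACE at 30% v PACE Plus at 18% has 56% power. Control at 30% v PACE at 18% has 55%.

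**Step 5: sensitivity.**

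- Cluster size at ICC 0.24, 30% v 18%, 267 per arm: 5 children per physician gives design effect 1.96 and power 64%; 9 children gives 2.92 and 48%.
- Difference with 80% power from 30%, 108 per arm: a fall of 15.8 points, slightly more than the 15-point fall reported for the previous study.
- ICC at which 30% v 18% drops to 80%: 198 per arm suffice under independence, so the design effect may reach 267/198 = 1.35, that is an ICC of 0.35/6.15 = 0.057.
- If 0.24 were a misprint for 0.024 (an assumption): design effect 1.15, effective 233 per arm, power 86% for 30% v 18% and 77% for 30% v 42%.
- Attrition: 801 is 1002 less 20%, not 25%. A 25% loss leaves 751.5, and power at ICC 0.24 is 53%, so this does not change the conclusion.

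**The case against.** Four things can be said for the plan.

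First, a reader might infer from the 90% for 30% v 18% that the 80% is simply a wrong number. The document does not support that. It speaks of a difference, not a fall, and 30% v 42% with continuity correction reproduces 267, 801 and 1002. That route runs against the hypothesized reduction and uses a second rate that is not stated, but its effect is to understate power for a fall. That is conservative and does no harm. This part of the objection stands in full.

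Second, the 80% is offered only under a declared assumption of no clustering. That is true, so the fault lies in the assumption and its justification, not in the arithmetic. But a declared assumption still has to agree with the evidence cited for it, and here it does not.

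Third, 0.24 may be a misprint, since the sentence calls it close to zero. This cannot be settled from the article. It makes the 54% conditional, but the sentence cannot stand either way: either the number or the conclusion drawn from it is wrong.

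Fourth, correlation will be adjusted for in analysis if needed. Adjustment protects the type I error rate but does not restore power. If 0.24 is right, the adjusted analysis is the one with about 54%.

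**Conclusion.** The point holds for clustering. At the printed physician ICC, the claim of 80% power for 12 points fails on every scenario tried: about 54% for 30% v 18%, 45% for 30% v 42%, and 43% for 50% v 38%. About 16 points would be needed for 80% power from 30%.

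These figures rest on 0.24 being correct as printed, on 112 physicians with equal cluster sizes (the planned number of physicians is not stated), and on a two-sided 0.05 test. For 30% v 18%, the range over 5 to 9 children per physician is 64% to 48%. A reader should not conclude that the trial is certainly underpowered: at an ICC below about 0.057 the stated 80% would be met for a fall from 30% to 18%.

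**What to change.** Rewrite the power paragraph and leave enrolment as it is.

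1. Check the physician-level ICC against the previous study's data.
2. If 0.24 stands, remove the statements that the ICCs are close to zero and that clustering is negligible. Then report either power for 12 points (about 54% for 30% v 18%; about 56% for PACE Plus v PACE and 55% for PACE v control with the actual split) or the fall from 30% that has 80% power (about 16 points).
3. If 0.24 is a misprint, print the correct value and recompute with the design effect. At an assumed 0.024 the results would be about 86% for 30% v 18% and 77% for 30% v 42%.
4. In either case, name both proportions, say that 12% means absolute points, and state the pairwise contrast, the test and any continuity correction, the number of physicians and the cluster size used.

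The cost is one rewritten paragraph and one look-up. No more patients are needed. If 0.24 is confirmed, the stated power becomes less favourable.

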### Physician and parent recruitment

#### *Physicians*

A total of 112 physicians were recruited in Atlanta, GA, the Bronx, NY and several communities in Michigan. To be eligible, physicians met the inclusion criteria outlined in Table 1. The sites chosen represented areas with a large African American and Hispanic/Latino populations being served by physicians that *did not* self-identify as African American and Hispanic/Latino.

**Table 1 T1:** Inclusion criteria for participation in current RCT

**Physician criteria**	**Patient criteria**	**Parent criteria**
1. Licensed physician in practice - board certified pediatrics/family medicine	1. Treated by the participating physician during the study intake period	1. Has primary responsibility for the child’s care
2. Treating children with asthma	2. Age 1–16 years	2. Self-identified as African American or Hispanic/Latino
3. Full-time (>25 hrs.) in a practice in GA, MI or NY	3. Diagnosis of asthma by a physician using NAEPP Guidelines (alternative descriptions such as reactive airway disease, bronchitis, or wheezy bronchitis were not accepted)	3. Has access to a telephone
4. Not Hispanic/Latino or African American in ethnicity/race (this allowed us to test the PACE Plus components that addressed cross cultural communication)	4. Has persistent asthma as defined by NAEPP classification for asthma severity	4. Consents to participate
5. Consented to participate	5. Does not have other chronic disorders that cause pulmonary complications, e.g. sickle cell disease	
6. Willing to generate a roster of pediatric African American and Hispanic/Latino asthma patients	6. Self-identify as African American or Hispanic/Latino	

To recruit physicians, a roster of potential physician participants was generated using membership lists from, e.g., local professional societies, asthma coalitions, and yellow-pages listings. Recruitment packets were initially mailed to potential candidates. The packet included a cover letter from the local physician co-investigator, a brochure describing the study, a brief screening form and questionnaire with a self-addressed, stamped envelope. Seven to ten days after the mailing, the recruitment coordinator called each physician office, spoke to a practice manager and arranged a day and time for the physician co-investigator to speak directly with the potential physician recruit. Personal contact by a local clinical practice leader was an important strategy for recruiting physicians [15-17]. Multiple visits and phone calls to physician offices and practice managers were not uncommon due to busy clinic schedules.

Physicians were told that participation involved generating a roster of their patients with asthma, completing 3 self-administered interviews over 2 years, and willingness to be randomly assigned to one of three study conditions. Every effort was made to minimize physician or office staff burden. For example, research-related meetings with office staff were kept to a minimum. All enrolled physicians received, a $50 gift card for completing each of the three data collection questionnaires and $50 for their office for providing a patient list in Year 1 and health care use data at the end of the study. Physicians randomized to either the PACE or PACE Plus interventions arms received 5 CME credits for completing the intervention sessions.

#### *Child and parent recruitment*

A total of 1,060 patients were recruited from the pool of patients provided by enrolled physicians. To be eligible, the child needed to meet the inclusion criteria listed in Table 1 and their parent or caregiver needed to meet the eligibility criteria as well.

Initially, the office staff of a participating physician was asked to provide a list of patients who met the eligibility criteria using office records. The patient list was provided to research staff. Eligible patients/caretakers were then mailed a recruitment packet containing a cover letter from the participating physician inviting them to enroll, a study overview page, two copies of the consent form, a health information screener form, a decline postcard, and a stamped self-addressed envelope for returning a copy of the consent and screener form.

Following the mailed information, patients received recruitment phone calls, which provided information about the study’s purpose, design, randomization, and data collection. Calls were made by trained bilingual staff, to ensure the same information was provided to all potential participants. Participants could opt to complete the consent and screener via paper and mail them back, via telephone with a trained staff member. Once consent was received by the research staff, parents were contacted by a telephone interviewer and scheduled for a baseline interview. The recruitment scripts, consent forms, and the telephone interviews were available in both English and Spanish. Children/parents subsequently followed physicians into one of the three study arms as randomized. Parents were not informed if their physician was participating in the intervention.

The following ongoing strategies were employed to enhance recruitment and retention. 1) caretakers received a $30 gift card following completion of the baseline data-collection interview and a $20 gift card for each subsequent completed follow-up interview; 2) Mother’s and Father’s Day cards were mailed annually to maintain a personal connection; 3) a study newsletter, mailed bi-annually, provided updates on study progress and basic asthma information; 4) repeated attempts were made over a year to check for reconnected phone lines; 5) the study team maintained contact with physician offices and periodically asked for updated contact information for enrolled participants.

### Randomization

#### *Experimental design and randomization*

A randomized controlled design was used in this study. At the beginning of the study, a permuted block randomization schedule was created using the RAN TBL and RANUNI functions in SAS to generate blocks of two for random assignment of physicians. Data are collected from three sites, Atlanta, Georgia, New York City, New York, and cities throughout Michigan. It is recognized that geographic site as well as size of practice of the physicians selected for study could impact on results. Thus, randomization was stratified by geographic area (three levels, Atlanta area, metropolitan New York, and Michigan) and size of practice (two levels, solo practice and multiple-physician practices). This randomization ensured that each type of practice and geographic area would be evenly distributed across the three arms of the study, which reduces bias due to these potentially confounding factors in the comparative analysis. Once physicians consented to participate, they were placed into one of the three arms of the study according to the randomization schedule with 44 physicians assigned to PACE, 36 to PACE PLUS and 32 to control (see sample size determination) with a total of 112 physicians and 1062 patients following those physicians into randomization.

Because this evaluation is being conducted for the purpose of recommending interventions for adoption, considerations about external validity of the results are important. One strength of this sample is that it includes physicians from practices in three large metropolitan areas. Thus, although the physician sample involved is not drawn from the entire U.S. population of clinicians, the study results will be somewhat representative of a wide variety of practice sites. Further, because background and practice characteristics of participating physicians will be assessed, it will be possible to make comparisons to the broader group of clinicians practicing in the U.S., as well as judgments about the extent to which the interventions are influenced by these characteristics.

Another threat to external validity, multiple–treatment interference, will be addressed by questionnaire items that will allow us to measure whether physicians have been involved in any other professional education efforts focusing on asthma care and education and cross-cultural communication training.

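### Permuted blocks of two cannot guarantee balance over three arms, and the 44/36/32 split does not fit the balance that the article says was ensured

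*Protocol article*

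**What the plan says.** The Methods/Design section sets out three arms: "This study used a randomized controlled design with three arms: control, the original PACE intervention, and PACE Plus intervention". Under Experimental design and randomization, the article describes a permuted block schedule programmed in SAS "to generate blocks of two for random assignment of physicians". It states that "randomization was stratified by geographic area (three levels, Atlanta area, metropolitan New York, and Michigan") and by "size of practice (two levels, solo practice and multiple-physician practices"), which makes 3 x 2 = 6 strata. It then draws the conclusion: "This randomization ensured that each type of practice and geographic area would be evenly distributed across the three arms of the study". The same paragraph reports the result, "with 44 physicians assigned to PACE, 36 to PACE PLUS and 32 to control (see sample size determination").

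The Sample size determination section gives no number of physicians and no allocation ratio. It works in children: 1002 at baseline, "taking into account a 25% attrition rate over 24 months leaving 801 total subjects at the end of the study".

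The Analysis section plans to compare the three groups on demographic and practice variables and to adjust if differences are found. It also plans adjusted models for variables related to outcome. It names several covariates, but geographic area and practice size are not among them.

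**The concern.** Stratified permuted blocks balance the arms within strata only if each complete block holds every arm in the intended ratio. For three equal arms the block length must be a multiple of three. A block of two has no room for the third arm, so completing a block restores no three-arm balance. The evenness that the article says was ensured is therefore a property that the described scheme does not have.

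The reported counts raise the same doubt from the other side. Arm totals are sums of stratum counts, so if every stratum had been split almost equally over the arms, the totals would be close to equal. They are 12 apart.

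This matters because the article itself calls area and practice size potential confounders and relies on the randomization to deal with them. If the blocking did not work as described, that safeguard is weaker than stated. The remaining one is adjustment triggered by baseline differences, in a section that does not name the two factors.

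**Working it through.** **Inputs.** Block length 2, three areas, two practice sizes, and 44/36/32 physicians (all from Experimental design and randomization); 112 physicians (Physicians section); 1002 and 801 children, 25% attrition, 30% baseline proportion with an ED visit, 12-point difference, significance level 0.05 (Sample size determination); 1,060 children recruited (Child and parent recruitment). Two-sided testing is assumed.

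**1. The article's own totals.** 44 + 36 + 32 = 112, as stated. Equal arms would give 112/3 = 37.3 physicians each.

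**2. Does the sample size section imply an unequal ratio?** 801/3 = 267 and 1002/3 = 334, both whole numbers. The continuity-corrected two-proportion formula for 30% versus 42% at 80% power gives exactly 267 per arm, hence 801 for three equal arms. The reported split reduces to 11:9:8 (dividing by 4), a ratio that appears nowhere in the article.

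**3. Largest possible gap under 1:1:1 blocks.** Only the last, incomplete block of a stratum can be unbalanced, and it adds at most (block length)/3 to the gap between two arms. Over six strata the limit is 6 x (block length)/3.

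| Block length | Theoretical limit | Simulated, 112 physicians in 6 strata |
|---|---|---|
| 3 | 6 | largest gap 6 |
| 6 | 12 | largest gap 9 |
| 9 | 18 | P(gap of 12 or more) below 0.0001 |
| 12 | 24 | P(gap of 12 or more) about 0.0003 |

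The simulations used 30,000 runs per setting, with equal and with random expected stratum sizes. The observed gap is 44 - 32 = 12. It is impossible with blocks of three. With blocks of six (reading two as two per arm) it requires all six strata to stop at the extreme in the same direction; the chance of exactly 44/36/32 is at most about 4 in 10 million.

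**4. Schemes without three-arm blocking.** Against simple 1:1:1 randomization, chi-square = (6.67² + 1.33² + 5.33²)/37.33 = 2.00 on 2 df, p = 0.37, and a gap of 12 or more has probability about 0.38. If each block of two held two different arms drawn at random, that probability is about 0.14. So the counts are unremarkable under schemes that do not enforce three-arm balance.

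**5. Effect on precision.** Take completers as 1060 x 0.75 = 795, shared in proportion to physicians: PACE 795 x 44/112 = 312, control 795 x 32/112 = 227. Equal arms would have 265 each. Power = Φ[(0.12 - 1.96 x SE0)/SE1], where SE0 uses the pooled proportion and SE1 the separate ones.

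- Control 30% (227) versus PACE 18% (312): SE0 = 0.03674, SE1 = 0.03739, power 90.0%.
- Equal arms, 265 each: SE0 = 0.03710, SE1 = 0.03673, power 90.1%.

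On physician numbers alone, 1/44 + 1/32 = 0.0540 against 2/37.33 = 0.0536 for equal arms. For PACE Plus versus PACE, 1/36 + 1/44 = 0.0505, slightly better than equal arms. These figures ignore clustering and serve only to compare the two splits.

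**The case against.** The strongest reply is that nothing has been shown to have gone wrong. Blocks of two can place physicians in three arms, for instance by drawing two different arms for each block, and a gap of 12 is then quite ordinary. The sentence on evenness concerns the mix of areas and practice types across arms, not equal arm totals; arms of 44, 36 and 32 could each have the same proportions from every stratum. An equal ratio for physicians is inferred from a calculation in children. The block length may be a misprint. The Analysis section already allows adjustment for practice variables and for variables related to outcome, and a fuller analysis plan may name the stratification factors.

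Most of this stands, and it limits the point. A reader might infer that the arms differ in area or practice size, or that the comparisons are biased. The article gives no counts by stratum, so neither follows. If two arms are drawn at random per block, each physician still has probability 1/3 for each arm in every stratum, and any imbalance is chance. A reader might also infer that assignments were predictable to those recruiting. With two of three arms per block, the first assignment rules out only one arm for the second, and nothing says that recruiters knew the block length or saw the schedule. Nor does the article suggest that the ratio changed over time.

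What the reply does not rescue is the guarantee. A scheme that merely permits 44/36/32 is not one that ensures evenness. A misprint for three or six would remove the conflict over block length but leave a split that such blocks cannot, or practically cannot, produce. A planned unequal ratio could reconcile the counts, but the section cited for them contains none. Condensation into an article does not explain it either, because the conflict lies between statements that are made, not in detail left out.

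**Conclusion.** The point holds as an inconsistency in the description of the allocation. The stated block length cannot deliver the stated balance, and the reported split (gap 12) does not fit 1:1:1 blocks of three (limit 6) or, in practice, of six. No stated unequal ratio accounts for it. This rests on two assumptions: that equal allocation of physicians was intended, which the sample size totals suggest but do not say, and that the six strata were used as described.

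It does not extend to a finding of stratum imbalance, bias or predictable assignment, for which the documents offer no evidence. The cost in power is negligible, about 0.1 percentage points for PACE versus control under the illustrative 30% versus 18%. What is at stake is whether the allocation was carried out as described, and whether the analysis should lean on a balance that the described method does not provide. It should be corrected, but it does not undermine the trial.

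**What to change.** 1. Check the executed SAS schedule and state the true block length and the intended allocation ratio. If the ratio was unequal by design, say so in the sample size section, so that the cross-reference leads to an explanation.
2. Replace the claim that evenness was ensured with a table of physician counts by arm, area and practice size.
3. Prespecify geographic area and practice size as fixed terms in every comparative model, in place of adjustment that depends on finding baseline differences.

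The cost is a schedule check, a few lines of corrected text, one small table and two covariates already recorded for stratification. No new data and no change to the conduct of the trial are needed.
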